### Outcomes {12} and data collection methods {18a}

#### Demographics, participant characteristics, and medical history

At an initial screening session prior to testing, participants will undergo a comprehensive medical history review and screening questionnaire. The medical history review will collect information about age, sex, race/ethnicity, height, weight, body mass index, employment status, alcohol and other drug use, medical cannabis use history (for phase 1 only), past/current treatments, and concomitant medications. Participant will also complete the Barratt Impulsiveness Scale (BIS) [16], Brief Pain Inventory (BPI; phase 1 only) [17], 36-item Short Form Health Survey (SF-36) [18], Depression, Anxiety and Stress Scale (DASS-21) [19], Dula Dangerous Driving Index (DDDI) [20], and the Driving Behaviour Questionnaire (DBQ) [21].

#### Driving performance metrics

The primary outcome measure for both phases of the trial is the standard deviation of lateral position (SDLP), a measure of lane weaving, swerving, and overcorrecting that is highly sensitive to alcohol and drug effects and is widely considered to be the gold-standard measure of driving performance in human psychopharmacology research [22–24]. SDLP and all secondary driving performance metrics are described below in Table 1. The analysis metric is change from pre-dosing to post-dosing (i.e. t2–t1 and t3–t1) for all measures.

**Table 1 Tab1:** Description of driving performance outcome measures

Domain	Measure	Outcome(s)
Driving performance (objective)	Standard deviation of lateral position (primary outcome)	Standard deviation of vehicle lateral position in centimetre (mean)
	Number of lane excursions	Number of times (count) one or more vehicle wheels exceeds the lane boundary
	Speed adherence	Mean speed (km/h) during driving, standard deviation of speed (km/h), and % time above the speed limit
	Steering variability	Steering reversal rate (number of directional changes per minute) and steering entropy (standard deviation of steering angle)
	Harsh acceleration	Count of rapid longitudinal acceleration events where acceleration is ≤ 0.35 g and < 0.58 g (harsh) or ≥ 0.58 g (very harsh)
	Harsh braking	Count of harsh braking events where deceleration is ≤ −0.75 g (extremely harsh), < −0.75g and ≤ −0.5g (very harsh) or ≤ −0.45g (harsh)
Ocular behaviour	Gaze behaviour (entropy)	Stationary gaze entropy and gaze transition entropy
	Rate and duration of visual fixations	Number of fixations (count per minute) and time of fixations (ms) where driver holds their gaze at a specific point on the roadway
	Microsleeps	Frequency (count) of long eye closures lasting ≥ 500 ms (NB: also adverse event indicator)
Driving performance (adverse event)	Instructor termination of drive	Number of times (count) a drive was terminated by the driving instructor
	Instructor intervention during drive	Number of times (count) the driving instructor had to intervene during a drive
Driving performance (subjective)	Instructor rating of fitness to drive	Instructor rating of fitness to drive (yes/no) at the end of each drive (proportion)

Driving-related outcome measures will be collected using two specially instrumented dual-control Mazda CX-5 research vehicles equipped with a proprietary automotive grade driver monitoring system and three GoPros to continuously and simultaneously monitor the forward roadway, the cabin interior, and the lane position of the vehicle. Drive terminations and assessor-rated driving performance will be scored by a qualified driving instructor who will always accompany participants while driving to ensure their safety.

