Phase 1 will involve 72 male and female patients (*n* = 36/*n* = 36) who are prescribed a THC-containing medical cannabis product (32 mg THC) to treat or manage chronic pain (*n* = 24), anxiety (*n* = 24), or insomnia (*n* = 24). These three conditions are the most common health indications for medical cannabis prescribing in Australia [1]. Patients will be further enrolled in a 1:1 ratio based on primary route of medical cannabis administration (inhaled or oral) and will complete assessments at different timepoints accordingly to account for differences in the pharmacokinetics and pharmacodynamics of inhaled and orally administered cannabinoid products [12]. This three-level stratification by gender, health condition, and route of administration will result in cell sizes of *n* = 6 (i.e. *n* = 6 males using an oral product for chronic pain), though this is for the purpose of maximising patient representation only and all patients will be treated as a single group for all primary statistical analyses. All patients will complete two testing days, including 1 day assessing highway driving ability and another day assessing urban driving skills. Treatments will be consumed by participants as prescribed by their physician in a supervised setting in the presence of a nurse.

Phase 2 (*healthy controls*) will involve 24 healthy male and female adults (*n* = 12/*n* = 12) who will complete a randomised, double-blind, placebo-controlled crossover trial to assess the effects of alcohol relative to placebo on real-world driving performance. Participants will complete two testing days per condition, 1 day assessing highway driving ability and another day assessing urban driving skills (i.e. four testing days total) during which they will receive alcohol (0.05% BAC) and placebo. Treatments will be administered orally (alcohol or placebo drink) using an established alcohol dosing formula in a supervised setting, with participants receiving treatments in a randomised and counterbalanced order.

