**Fig. 1 Fig1:**
[figure not shown]
SPIRIT figure — schedule of enrolment, interventions, and assessments

For patients using oral products (*n* = 36), drive 1 will occur prior to medical cannabis self-administration, with drives 2 and 3 occurring 1.25 and 3 h after medical cannabis self-administration. For patients using inhaled products (*n* = 36), drive 1 will occur prior to medical cannabis self-administration, with drives 2 and 3 occurring 0.5 and 2.25 h after medical cannabis self-administration. Informed by prior work [13], drives 2 and 3 both fall within the potential window of impairment associated with inhaled and orally administered THC, with drive 2 corresponding to the expected period of peak effects, when impairment—if present—is likely to be greatest [14]. Blood and oral fluid samples will be collected immediately prior to each drive. An impairment assessment battery comprising cognitive testing and subjective drug effect questionnaires (see Outcomes {12}) will be administered immediately following each drive.

#### Phase 2

In phase 2, participants will first complete a practice session and a baseline drive before completing four separate days of testing, including two test days at AARC and two test days at METEC. Due to the remote location of the AARC test track, participants will be transported by the research team and will stay in a hotel for 2 nights before each of the two AARC test days before being transported back to Melbourne on the afternoon of the second AARC test day. Participants will then, in that same week, complete the two test days at METEC. Given the considerable logistical complexities associated with testing at remote locations, and to minimise potential dropouts, test days will be scheduled to occur back to back, meaning the washout period between test days will be minimal but within the expected metabolic elimination window for acute low doses of alcohol. As in phase 1, participants will complete three driving assessments within each test day, including a baseline drive in the morning (drive 1) followed by a second drive at the time of expected peak alcohol impairment (drive 2) and a third drive when impairment is expected to be subsiding (drive 3). The test day schedule (see Fig. 1) will be identical for each of these four testing days. The order in which participants receive alcohol and placebo at the two tracks will be randomised and counterbalanced.

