### Sample size {14}

For phase 1, a sample size of *n* = 72 will allow us to detect a small magnitude change (*f* = 0.15) in our primary outcome measure—the standard deviation of lateral position—with 90% power assuming one group (i.e. all patients collapsed into a single group), six repeated measurements (three drives over 2 days), an estimated correlation among repeated measures of 0.6, and a non-sphericity correction of 0.6. The effect size used for this power calculation was derived from a previous on-road driving study with synthetic THC (dronabinol) [15] and conservatively reduced to account for the fact that treatment effects associated with prescribed medical cannabis may be considerably smaller than those seen previously in healthy volunteers given an intoxicating dose of THC. For phase 2*,* a sample size of *n* = 24 will allow us to detect a medium effect size (*f* = 0.25) with 90% power assuming one group, 12 repeated measurements (12 drives over 4 days of testing), an estimated correlation among repeated measures of 0.5, and a non-sphericity correction of 0.6. This effect size (*f* = 0.25) is equivalent to the level of impairment considered meaningful in a recent meta-analysis of 80 publications comprising 1534 driving or cognitive performance outcomes [13]. All sample size calculations were done in G*Power 3.1.

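### Phase 2 analyses change from the same-day drive 1; adjusting for drive 1 instead would give the alcohol-placebo contrast a smaller variance, by a factor of about 1.1 to 2.0

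*Protocol article*

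**What the plan says.** Under *Driving performance metrics* the protocol article sets one metric for SDLP and every secondary driving measure in both phases: "The analysis metric is change from pre-dosing to post-dosing (i.e. t2–t1 and t3–t1) for all measures". The sections on CANTAB and on subjective assessments repeat change from t1 for those outcomes.

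Phase 2 has 24 healthy adults "who will complete a randomised, double-blind, placebo-controlled crossover trial to assess the effects of alcohol relative to placebo on real-world driving performance" (*Trial design*). Each has four test days, alcohol and placebo at each of two tracks, with three drives a day. Drive 1 is before dosing. Test days are back to back, "meaning the washout period between test days will be minimal" (*Participant timeline*, Phase 2).

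*Sample size* states that "a sample size of *n* = 24 will allow us to detect a medium effect size (*f* = 0.25) with 90% power assuming one group", with "12 repeated measurements (12 drives over 4 days of testing" and then "an estimated correlation among repeated measures of 0.5, and a non-sphericity correction of 0.6". *Statistical analysis* names linear mixed-effects models for continuous data. It neither names nor excludes a baseline covariate.

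**The concern.** Phase 1 has no placebo, so change from drive 1 is the natural measure of effect there. Phase 2 has a placebo day for every participant at each track. As the metric is written, the Phase 2 contrast is (A2 − A1) − (P2 − P1), where A and P are the alcohol and placebo days and 1 and 2 are the drives. Subtracting drive 1 fixes its weight at one, whatever its correlation with drive 2. A covariate lets the data set that weight.

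Phase 2 supplies the alcohol reference against which the cannabis results will be read. With 24 participants, avoidable noise widens the interval around that reference. The 90% power was also computed for 12 raw drives, not for the alcohol-placebo difference in change, so it does not describe the contrast that would be reported.

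**Working it through.** **Reproducing the plan's figure.** Inputs from *Sample size*: n = 24, m = 12, f = 0.25, ρ = 0.5, ε = 0.6; two-sided α = 0.05 from *Statistical analysis*. The G*Power formula for one group and within factors is λ = f²·n·m·ε/(1 − ρ), with df1 = (m − 1)ε and df2 = (n − 1)(m − 1)ε.
- Phase 2: λ = 0.0625 × 24 × 12 × 0.6/0.5 = 21.6, df 6.6 and 151.8, power 94.1%. For 90% power, n = 21 is enough, so 24 is conservative.
- Phase 1 as a check of the formula (n = 72, m = 6, f = 0.15, ρ = 0.6, ε = 0.6): λ = 14.58, power 90.3%, which matches the article.

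**Variance of the contrast.** Take unit SD per drive, same-day correlation r_s, and correlation r_b between drives on different days at the same track. Per participant and track:
- Post-dose only, A2 − P2: 2(1 − r_b)
- Change, (A2 − A1) − (P2 − P1): 4(1 − r_s)
- Adjusted for the baseline difference A1 − P1: 2(1 − r_b) − [2(r_s − r_b)]²/[2(1 − r_b)]

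**Choice of correlations.** The article gives one ρ and one ε, not r_s and r_b. ε = 0.6 rules out equal correlation among all 12 drives, because that gives ε = 1. I therefore held the mean correlation at 0.5, let same-day drives correlate more strongly, and gave all different-day pairs one value, so r_b = (5.5 − 2r_s)/9:

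| r_s | r_b | implied ε | post only | change | adjusted | change/adjusted |
|---|---|---|---|---|---|---|
| 0.50 | 0.500 | 1.00 | 1.00 | 2.00 | 1.00 | 2.00 |
| 0.60 | 0.478 | 0.90 | 1.04 | 1.60 | 0.99 | 1.62 |
| 0.70 | 0.456 | 0.70 | 1.09 | 1.20 | 0.87 | 1.38 |
| 0.75 | 0.444 | 0.60 | 1.11 | 1.00 | 0.78 | 1.29 |
| 0.80 | 0.433 | 0.51 | 1.13 | 0.80 | 0.66 | 1.21 |
| 0.90 | 0.411 | 0.37 | 1.18 | 0.40 | 0.37 | 1.09 |

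The row r_s = 0.75 meets both stated inputs. So does a second pattern, clustering by track: correlation 0.63 among all drives on a track and 0.39 between tracks gives mean ρ = (30 × 0.63 + 36 × 0.39)/66 = 0.50 and ε ≈ 0.6. There r_s = r_b, so change has variance 4 × 0.37 = 1.48 per track, adjustment 2 × 0.37 = 0.74, and the ratio is 2.00.

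**Power.** I assumed a 0.5 SD alcohol effect at drive 2 (f = 0.25 read as a two-level contrast), averaged over both tracks. In these patterns averaging halves the variance. Power is from the noncentral t at n = 24, with 22 df for change, and 21 df plus a 5% variance penalty for adjustment:

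| Pattern | change | adjusted |
|---|---|---|
| All drives equally correlated at 0.5 (ε = 1) | 65% | 90% |
| Track clustering (ε ≈ 0.6) | 78% | 96% |
| Same-day clustering (ε = 0.6) | 91% | 96% |

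In the equal-correlation pattern, 90% power on change would need 45 participants.

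**Cost of adjustment.** In 20,000 simulated trials at n = 24 with all correlations 0.5, the variances were 0.99 (post only), 2.02 (change) and 1.03 (adjusted). Putting same-day drive 1 alone into a random-intercept model gave 1.16; adding the participant's mean drive 1 gave 1.02 (1,000 trials).

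**The case against.** **The loss may be small.** This stands. If day-to-day variation dominates, change is only modestly worse than adjustment, and from r_s = 0.75 upward in the first table it has a smaller variance than post-dose values alone. A reader might infer that the plan's own correlation implies a doubling, or that subtracting drive 1 only ever adds noise. The article supports neither. Doubling is compatible with ρ = 0.5 and ε = 0.6 but is not forced by them.

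**The analysis plan may already adjust.** Change with drive 1 as covariate gives the same treatment estimate as the post-dose value with drive 1 as covariate, so the loss arises only without adjustment. The metric also cannot be the literal response in the Poisson, negative binomial and logistic models planned for counts and yes/no outcomes, so it may be meant as a contrast. This limits the point to continuous outcomes. It does not remove it: the article publishes change as the metric and names no adjustment.

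**A common metric keeps the phases comparable.** This is a fair aim. Reporting raw change descriptively meets it.

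**Carry-over.** A reader might argue that back-to-back days make change the riskier choice, because an after-effect of alcohol on the next morning's drive 1 enters it at full weight. The argument cuts both ways: an after-effect lasting all day cancels in a change score but not in a post-dose comparison. The article does not show that any after-effect exists, so this is no ground for preferring either metric.

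**Conclusion.** The point holds as one of efficiency. In every correlation pattern examined, adjusting for drive 1 gave a smaller variance for the Phase 2 alcohol-placebo contrast than the unadjusted change score. The factor is 2.0 when all drives on a track are equally correlated, about 1.3 when same-day clustering alone explains ρ = 0.5 and ε = 0.6, and about 1.1 when same-day correlation reaches 0.9.

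The power figures rest on three assumptions not in the article: a 0.5 SD effect, averaging over both tracks, and the correlation patterns shown. The change metric causes no bias that the article demonstrates, and the sample size is not too small on its own formula. Nor is the better method free, as a reader might suppose, but its cost is small.

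**What to change.** For Phase 2 continuous outcomes, state before the unblinded analysis that the alcohol-placebo contrast at drives 2 and 3 is estimated from a mixed model with same-day drive 1 and the participant's mean drive 1 as covariates, and with test day or period in the model. Adjusting for the within-participant difference in drive 1 is equivalent. The participant mean should not be left out: without it the simulated variance rose from 1.02 to 1.16. Report raw change from drive 1 descriptively, for comparison with Phase 1.

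A model that constrains the alcohol and placebo pre-dose means to be equal should serve at most as a sensitivity analysis. An after-effect of the previous day's alcohol would violate that constraint.

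The cost is one sentence of analysis text, one degree of freedom and about 3-5% of variance at n = 24. It needs no new data and changes nothing for participants.

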##### Cambridge Neuropsychological Test Automated Battery (CANTAB)

Participants will complete three cognitive tests drawn from the CANTAB (Cambridge Neuropsychological Test Automated Battery, Cambridge Cognition, Ltd., UK) system designed specifically for neuropsychological testing and academic research. Tests include (1) Rapid visual information processing (RVP), an assessment of sustained attention; (2) reaction time (RTI), an assessment of motor and mental response speed and accuracy; and (3) spatial working memory (SWM), a visuospatial working memory task with notable executive function demands. Cognitive data will be analysed as change from t1 to t2 and from t1 to t3. All CANTAB assessments will be administered on an iPad in a quiet area of the testing site. Each task and its associated outcome measures are described below in Table 2:

**Table 2 Tab2:** Description of CANTAB tests being used to assess cognitive function

Task	Measure	Outcomes
Rapid Visual Information Processing (RVP)	A sensitive measure of sustained attention (focus) which is integral to safe driving behaviour	A prime: A measure of signal detection sensitivity to the target sequence. Higher scores indicate better performance Response latency: The median response time (ms) for correctly identified target sequences Probability of false alarm: The proportion of incorrect responses, calculated as the number of false alarms divided by the total number of false alarms plus correct rejections
Reaction time (RTI)	Measures motor and mental response speed, including reaction time, and response accuracy. Relates to driver ability to respond quickly and appropriately to visual stimuli	Reaction time: Median time (ms) taken to release the response button after stimulus presentation. Calculated across correct trial Total errors: Total number of trials in which a response error occurred
Spatial working memory (SWM)	Measures visuospatial working memory, placing demands on executive function and assessing strategy use and errors. Reflects visual search efficiency in drivers as well as executive function which incorporates key cognitive skills	Between errors: Number of times a participant revisits a box where a token was previously found. Calculated across four, six, and eight token trials Strategy (6–8 boxes): Number of times a participant starts a new search from the same box they started with previously. Lower scores indicate greater strategy use

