### Statistical analysis {20a, 20b, 20c}

Participant demographic and baseline characteristics will be summarised separately by study phase and treatment condition, where applicable. Continuous variables will be summarised using means and standard deviations (SD), and where appropriate, medians and interquartile ranges (IQR) will also be reported. Categorical variables will be summarised using frequencies and percentages (%). No formal hypothesis testing of demographic variables will be conducted; summaries are intended to describe the study population and assess baseline comparability across groups. Analysis of primary and secondary outcome measures will be conducted using a series of linear mixed-effects models (continuous data), Poisson or negative binomial generalised linear mixed models (count data), logistic mixed-effects models (binary data), or time-binned mixed models and linear regression (ocular data). Post hoc tests with Bonferroni adjustments will be conducted where significant main effects or interaction effects are observed. No deletion or imputation will be used where data is missing at random, as mixed models inherently accommodate incomplete repeated measures. Sensitivity analysis will be conducted using delta-adjustment for nonrandom missing data. Exploratory subgroup analyses will test for differences in change in outcome measures over time as a function of health condition, route of administration, and gender (phase 1 only). All statistical analyses will be conducted using SPSS (IBM Corp, Armonk, NY, USA) and R, and tests will be set two-tailed with a conventional level of significance of *p* < 0.05.

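### The Table 1 inequalities for harsh acceleration and very harsh braking do not define the bands they name, so two secondary driving outcomes are wrong as written

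*Protocol article*

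**What the plan says.** The protocol article, under Driving performance metrics, states that "SDLP and all secondary driving performance metrics are described below in Table 1". Two rows of that table define event counts by thresholds in g.

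- **Harsh acceleration.** The outcome is a "Count of rapid longitudinal acceleration events" with two classes: "acceleration is ≤ 0.35 g and < 0.58 g (harsh) or ≥ 0.58 g (very harsh").
- **Harsh braking.** There are three classes: "deceleration is ≤ −0.75 g (extremely harsh), < −0.75g and ≤ −0.5g (very harsh) or ≤ −0.45g (harsh").

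The same section says every driving measure is analysed as the difference between each post-dose drive and the pre-dose drive. The Statistical analysis section assigns counts to "Poisson or negative binomial generalised linear mixed models (count data"). No other part of the article restates or corrects the cut-offs.

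Table 2, in the CANTAB section, describes the spatial working memory strategy outcome as follows: "Number of times a participant starts a new search from the same box they started with previously. Lower scores indicate greater strategy use".

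**The concern.** For a count outcome the threshold is the outcome: it decides which events enter the model. In both Table 1 rows a class that should lie between two cut-points is written with both inequalities pointing the same way. One of them is then redundant and the class is no longer a band.

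If the rules were programmed as printed, harsh acceleration would be dominated by normal driving, and two of the three braking classes would hold almost the same events. If the code uses other bands, the published definition will not match the analysis, and a reader cannot confirm from the article that the thresholds used were those fixed in advance.

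**Working it through.** **Inputs.** All cut-points come from Table 1: 0.35 g and 0.58 g for acceleration; −0.75 g, −0.5 g and −0.45 g for braking. Braking is read as signed acceleration, as the minus signs imply. There is no stated result to reproduce, so the check is whether the classes cover the range and separate it.

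**Acceleration, as written**

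- *Harsh*: {a ≤ 0.35} ∩ {a < 0.58} = {a ≤ 0.35}.
- *Very harsh*: {a ≥ 0.58}.
- Unclassed: 0.35 < a < 0.58. On a 0.001 g grid this is every value from 0.351 to 0.579.

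| a (g) | As written | If the first sign is ≥ |
|---|---|---|
| 0.05, 0.10, 0.20 | harsh | none |
| 0.35 | harsh | harsh |
| 0.36, 0.45, 0.57 | none | harsh |
| 0.58, 0.70 | very harsh | very harsh |

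**Braking, as written**

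- *Extremely harsh*: {a ≤ −0.75}.
- *Very harsh*: {a < −0.75} ∩ {a ≤ −0.5} = {a < −0.75}. This differs from *extremely harsh* only at exactly −0.75 g.
- *Harsh*: {a ≤ −0.45}, with no bound on the severe side, so it contains both other classes.

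| a (g) | As written | If *very harsh* is > −0.75 and ≤ −0.5, and classes are exclusive |
|---|---|---|
| −0.44 | none | none |
| −0.45, −0.48 | harsh | harsh |
| −0.50, −0.60, −0.74 | harsh | very harsh |
| −0.75 | extremely harsh, harsh | extremely harsh |
| −0.76, −0.90 | all three | extremely harsh |

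Reading the braking signs as magnitudes does not rescue the row. *Extremely harsh* would then be 0.75 g or less and *very harsh* 0.5 g or less, which takes in gentle braking and reverses the order of severity.

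The set {a ≤ −0.45} is well defined under every signed reading, so the total braking count survives. What is lost is the division by severity.

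**Strategy score (Table 2).** No arithmetic applies. One sentence counts repeated starts from a single box: "Number of times a participant starts a new search from the same box they started with previously". The next gives the direction: "Lower scores indicate greater strategy use". They sit awkwardly together if restarting from the same box is the strategic behaviour, but the article does not say whether it is.

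**The case against.** Four points can be made on the other side.

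1. **The intent is recognisable.** The row is titled harsh acceleration, it speaks of rapid events, and the next class starts at 0.58 g. A reader would see a flipped sign, and code that flagged all ordinary acceleration as harsh would soon be noticed. Nothing shows that the vehicle system's event extraction was built from this table. This stands: miscounting is conditional on literal programming. It does not make the printed definition right, and this is an explicit rule stated wrongly, not detail left to another document.

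2. **It could be a symbol lost in typesetting or text extraction.** This cannot be excluded. However, the other acceleration sign (≥ 0.58 g) is printed correctly in the same cell, and the braking row repeats the fault with different symbols.

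3. **An open-ended *harsh* braking class may be deliberate.** A threshold at or below −0.45 g can be a nested, cumulative class. This stands: the missing far bound is not in itself an error. A reader might infer that one event at −0.80 g would be counted three times, but that needs the three classes to be summed, and the article does not say they are.

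4. **The strategy score need not be inverted.** A reader might infer from Table 2 that the sign of the strategy effect is reversed. That requires the premise that same-box restarts are the strategy, which the article does not state. If the description is loose and the stated direction is right, the score will be read correctly. This stands, and the item is only a query.

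**Conclusion.** The two Table 1 definitions are wrong as written. *Harsh* acceleration takes in everything at or below 0.35 g and leaves the band strictly between 0.35 and 0.58 g unclassed. *Very harsh* braking duplicates *extremely harsh* apart from the single value −0.75 g, and events above −0.75 g and at or below −0.5 g lose their intended label while still counting as *harsh*. These conclusions follow from the printed inequalities alone, taking braking as signed acceleration.

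The consequence is limited. Both outcomes are secondary. SDLP is the primary outcome in both phases, the sample size calculations do not rest on these counts, and the primary analysis is untouched. Wrong counts would follow only if the printed rules were used literally, which the article neither shows nor rules out. This is a lower-severity correction of secondary-outcome definitions. Neither triple counting of braking events nor a reversed strategy score is shown.

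**What to change.** Correct Table 1, keeping every printed cut-point; the sponsor should confirm that these are the intended bands:

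- *Harsh* acceleration: ≥ 0.35 g and < 0.58 g. *Very harsh* stays at ≥ 0.58 g.
- *Very harsh* braking: > −0.75 g and ≤ −0.5 g. *Extremely harsh* stays at ≤ −0.75 g.
- *Harsh* braking: state whether ≤ −0.45 g is cumulative or limited to > −0.5 g and ≤ −0.45 g.

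Then confirm that the event-extraction code applies these bands. Separately, check the strategy description in Table 2 against the software output, and amend the description or the direction if they disagree.

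The cost is a table correction and a code check. No new data are needed, and both can be done before the driving data are analysed.
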